### 2.4. Data Collection and Management

Personal patient data remain at the participating centers. Pseudonymized clinical data (according to the data collection schedule set out in Table 2) were captured by an electronic case report form which can be reached via a secure website. To enter the data, investigators used a confidential and personalized login and password. The electronic case report form was designed to allow automatic and manual checks for plausibility and completeness. Each active site was visited, and all patients were monitored according to a predefined monitoring plan by the Contract Research Organization of the study (IPPMed; Institute for Pharmacology and Preventive Medicine GmbH, Cloppenburg, Germany or a respective representative). Per routine, monitoring visits confirmed that informed consent was obtained and checked that values recorded in the electronic case report form matched source documents. Data were also statistically audited using the method of Carlisle [22] and similar approaches. Pseudonymized data are accessible to the participating center, the principal investigator, and IPPMed or its authorized representatives. Pseudonymized data will be stored in the database for 10 years unless legal requirements demand longer storage. Adverse event data were sent to the competent national authorities and ethics committees involved. Protocol modifications were reported to ethics committees, investigators, and ClinicalTrials.gov. Clinical data from the registry will be published or presented using pseudonymized data only.

### 2.5. Statistics

The sample size was estimated based on published data. A randomized controlled trial reported a TWA MAP < 65 mmHg of 0.44 mmHg (25% and 75% percentiles, 0.23 and 0.72 mmHg) without and 0.10 mmHg (25% and 75% percentiles, 0.01 and 0.43 mmHg) with HPI monitoring [18]. Considering the wide interquartile range of TWA MAP < 65 mmHg, we planned to include at least 700 evaluable patients in this registry.

Statistical analysis will be performed for the total registry population, as well as for subgroups. We will perform descriptive analyses to describe and quantify intraoperative hypotension, patient characteristics, and perioperative data. For continuous variables, means with standard deviations will be presented for normally distributed data and medians with 25th and 75th percentiles for non-normally distributed data. For categorical variables, numbers and percentages will be shown. Patients with missing data will be excluded from the analysis. All statistical analyses will be performed using IBM SPSS Statistics (IBM, Armonk, NY, USA) or R Core Team (Version 4.2.1; R Core Team/R Foundation for Statistical Computing, Vienna, Austria; https://www.R-project.org/; date accessed: 19 September 2022).

### 2.6. Data Monitoring

There were no monitoring visits prior to site and patient enrollment. Physicians and registry personnel were required to make themselves familiar with the registry protocol, eCRF, requirements, and procedures.

According to a predefined monitoring plan, a fixed percentage of sites were randomly selected and monitored by IPPMed. In these centers, source data verification was performed according to a pre-specified monitoring plan. If findings from data management will raise doubts with regard to data quality at a specific site, additional monitoring visits may be performed (risk-based monitoring).

## 3. Discussion

With the data from this registry, we will describe the incidence, duration, severity, and causes of intraoperative hypotension when using HPI monitoring in patients having elective major non-cardiac surgery. The HPI software uses machine learning to predict hypotension from changes in blood pressure waveform features.

Intraoperative hypotension has been identified as a common and potentially modifiable risk factor for postoperative organ injury in patients having non-cardiac surgery [10,11]. Anesthesiologists should, therefore, consider avoiding intraoperative hypotension as a mainstay of intraoperative hemodynamic management. However, avoiding intraoperative hypotension is challenging [12] because hypotension can have numerous causes, including vasodilation due to anesthetic drugs or systemic inflammation, hypovolemia due to bleeding, or low cardiac output due to impaired cardiac contractility. The pathophysiological rationale behind using machine learning-based predictive monitoring is that predicting hypotension before it becomes clinically apparent may allow preemptive or timely treatment and help avoid hypotension [13]. This pathophysiological rationale is reasonable because hypotension is preceded by subtle hemodynamic changes that are imperceptible for the human eye and current monitoring methods [23,24]. Real-time hemodynamic monitoring combined with machine learning may identify these subtle hemodynamic changes preceding hypotension [11,23,24,25].

Machine learning, in general, is the study of computer algorithms that automatically learn and improve with experience using large data sets and thus allowing the identification and analysis of features from a vast amount of data. Over the past decade, the development and application of machine learning algorithms across a range of industries—including healthcare—has grown substantially. Using machine learning to predict hemodynamic instability is an intriguing approach that has the potential to initiate a paradigm shift in hemodynamic monitoring and management—from reactive to predictive monitoring and proactive management.

The HPI algorithm was developed by Hatib and co-workers [14] for the real-time prediction of hypotension. The HPI algorithm was modeled and cross-validated in 1334 surgical and critically ill patients using 545,959 min of arterial blood pressure waveform recordings and 25,461 episodes of hypotension [14]. It was externally validated in 204 surgical patients [14]. The HPI predicts hypotension—in the current version defined as a MAP < 65 mmHg for at least 1 min—from 23 individual arterial blood pressure waveform features (that were identified from 3022 individual and 2,606,147 combinatorial waveform features) [14].

Validation studies in surgical patients suggest that the HPI may predict hypotension 15 min before the event with a sensitivity and specificity of more than 80% [14,26]. HPI-guided blood pressure management reduced intraoperative hypotension compared to routine care in small preliminary trials in patients having hip arthroplasty [27] and general non-cardiac surgery—but not in a trial randomizing 212 non-cardiac surgery patients to HPI-guided or routine blood pressure management [28].

We included consenting adults having elective major non-cardiac surgery with general anesthesia in whom arterial catheter placement and HPI monitoring was planned for clinical indications independent of the study. We used duration of surgery (at least 120 min) to select patients having major surgery who are at particular risk of developing hypotension. Although the HPI algorithm also works on blood pressure waveforms recorded non-invasively using a finger-cuff device [29,30], we only included patients in whom blood pressure is monitored invasively using an arterial catheter because intraarterial blood pressure monitoring remains the clinical reference method [31]. Patients having emergency surgery were not included because these patients would not have enough time to provide informed consent. Patients with atrial fibrillation were not included because the HPI algorithm is not validated in patients with atrial fibrillation. Sepsis causes marked alterations in cardiovascular dynamics—including alterations in vasomotor tone and blood pressure regulation. We, therefore, also excluded septic patients from the registry.

To quantify intraoperative hypotension, we will report the TWA MAP < 65 mmHg—i.e., the area under a MAP of 65 mmHg divided by the total duration of surgery [17,18]. TWA MAP reflects the combination of the duration and severity of hypotension—and thus is a measure of hypotension that is clinically meaningful. In a preliminary randomized trial, the median TWA MAP < 65 mmHg was 0.44 mmHg without HPI monitoring and 0.10 mmHg with HPI monitoring [18]. However, TWA MAP is not routinely used in clinical practice and, thus, clinicians will not be familiar with this measure. We will, therefore, also describe measures of hypotension that are frequently used in clinical practice—including the number of episodes below certain MAP thresholds and the proportion of patients with at least one episode (1 min or more) below certain MAP thresholds.

Intraoperative hypotension can have different causes [10,32]. A detailed understanding of underlying causes could allow treating intraoperative hypotension causally with specific interventions. We will, therefore, also assess causes of intraoperative hypotension by analyzing advanced hemodynamic variables during hypotensive episodes (including cardiac output, stroke volume, heart rate, systemic vascular resistance, and pulse pressure variation).

The goal of any intraoperative hemodynamic monitoring and management strategy is to improve postoperative patient-centered outcomes. The registry will not have sufficient power to investigate the effect of HPI monitoring on patient-centered outcomes. Nevertheless, we will describe the incidence of postoperative acute myocardial and kidney injury, postoperative death, hospital re-admission, and a composite outcome of non-fatal cardiac arrest and death on an exploratory basis. We considered stroke as potential further outcome as it is a major posteroperative complication. However, overt (not covered) postoperative strokes occur rarely compared to other major postoperative complications. Additionally, there are conflicting data on a potential association between intraoperative hypotension and postoperative stroke in non-cardiac surgery patients (with many studies indicating that there is no strong association [2,33,34]). Finally, we discussed whether delirium is a potentially valuable outcome. Although it is common, the initial diagnosis of delirium mostly relies on suspicion, and often will go undetected or is misdiagnosed. Furthermore, a thorough clinical evaluation is considered the gold standard for its diagnosis, and there is no biomarker with high sensitivity and specificity. However, investigating postoperative delirium would require assessing patients several times a day during the first postoperative days. Although European Guidelines [35] advocate the post-operative assessment of delirium, it was decided not to document it in the current study.

While a randomized trial would have been desirable, available data on intraoperative hypotension when HPI monitoring is used in a multicenter setting in Europe are scarce. As such, there was a lack of data for a sample size calculation and further observational data were required. The results of this registry study will inform the design of future randomized trials investigating whether HPI-guided blood pressure management improves patient-centered outcomes in patients having surgery compared to routine blood pressure management. Specifically, the registry will provide event rate estimates necessary for robust sample size estimations for randomized trials.

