### 2.2. Patients

We planned to include at least 700 evaluable patients in the registry. We included consenting adults (≥18 years) who were scheduled for elective major non-cardiac surgery under general anesthesia that was expected to last at least 120 min and in whom arterial catheter placement and HPI monitoring was planned for clinical indications. We did not include patients having emergency surgery, nephrectomy, and liver or kidney transplantation; patients with atrial fibrillation and/or sepsis (according to current Sepsis-3 definition); patients with American Society of Anesthesiology physical status classification V or VI; patients who were not able to understand the nature, significance, and scope of the investigation; pregnant women; patients without signed informed consent/data protection statement; and patients participating in interventional trials.

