Acute myocardial injury was defined as an increase in high-sensitivity troponin concentration within the first three postoperative days according to the definition of “myocardial injury and infarction associated with non-cardiac procedures” set forth in the Fourth Universal Definition of Myocardial Infarction (2018) [19]. We considered high-sensitivity troponin T or I values (whichever was used in each center) when measured per routine care before surgery (baseline) and on postoperative days 1, 2, or 3.

Acute kidney injury was defined based on “Kidney Disease: Improving Global Outcomes Clinical Practice Guideline for Acute Kidney Injury” [20,21] as (a) an increase in serum creatinine concentration of ≥0.3 mg/dL within any 48-h period within the first 7 postoperative days, (b) an increase in serum creatinine of ≥50% from baseline within the first 7 postoperative days, or (c) the need for renal replacement therapy within the first 7 postoperative days. We considered serum creatinine values when measured per routine care before surgery (baseline) and on postoperative days 1 to 7. We only considered the creatine and renal replacement criteria (i.e., excluding the urine output criterium) in accordance with current recommendations [20,21] because urine output is usually not reliably recorded in patients after surgery.

Non-fatal cardiac arrest was defined as successful resuscitation from ventricular fibrillation, ventricular tachycardia, asystole, or pulseless electrical activity requiring cardiopulmonary resuscitation, pharmacological therapy, or cardiac defibrillation.

Further, we will describe the intensive care unit length of stay and hospital length of stay. It will be documented whether an institutional hemodynamic protocol was available.

We will compare the incidence, duration, and severity of intraoperative hypotension observed in patients in the present registry with those reported in previous observational and interventional studies using similar metrics quantifying intraoperative hypotension and reporting postoperative complications (“historical data” from studies published in international peer-reviewed journals).

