We will also compare the incidence, duration, and severity of intraoperative hypotension observed in patients in the EU-HYPROTECT registry with those observed in patients in whom HPI monitoring was not used. Hemodynamic data from such patients are available to Edwards Lifesciences because they are being shared under the umbrella of different joint projects between Edwards Lifesciences and hospitals using Edwards Lifesciences monitoring (data share agreements are in place with all institutions sharing patient data).

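### The laboratory event rates promised for robust sizing of future trials will be tested-only rates from an HPI-only cohort, and the Discussion does not say so

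*Protocol article*

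**What the plan says.** All places are in the Protocol article.

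- **3. Discussion.** The results are to inform randomised trials of whether HPI-guided management "improves patient-centered outcomes in patients having surgery compared to routine blood pressure management". The paragraph ends with the claim that "the registry will provide event rate estimates necessary for robust sample size estimations for randomized trials". The same section calls the outcomes exploratory and concedes low power for the effect of HPI on them. It does not qualify the rates themselves.
- **2.3. Objectives and Outcomes, myocardial injury.** High-sensitivity troponin T or I, depending on the centre, is used "when measured per routine care before surgery (baseline) and on postoperative days 1, 2, or 3".
- **2.3, kidney injury.** "We considered serum creatinine values when measured per routine care before surgery (baseline) and on postoperative days 1 to 7". Need for renal replacement therapy also qualifies.
- **2.5. Statistics.** "Patients with missing data will be excluded from the analysis".
- **2.2. Patients.** The cohort consists of adults "in whom arterial catheter placement and HPI monitoring was planned for clinical indications".
- **2.3, comparisons.** One comparison is with published studies and concerns hypotension. The other begins "We will also compare the incidence, duration, and severity of intraoperative hypotension observed in patients in the EU-HYPROTECT registry with those observed in patients" and continues to patients without HPI monitoring, for whom haemodynamic data are said to be available.
- **2.3, follow-up.** Death, re-admission and the arrest/death composite are followed to day 30, by phone after discharge.

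**The concern.** A sample size for a two-arm trial with a binary outcome needs two things: the event rate under control management and the effect to be detected. The rate must also describe the population to be randomised.

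The registry's laboratory rates fall short on both counts. First, the denominator is the set of patients whom clinicians chose to test. If sicker patients, certain centres or longer stays lead to more testing, the tested-only rate is higher than the cohort rate. Second, the rate belongs to HPI-monitored patients, whereas the control arm of the trial described would have routine management. A planner who takes the sentence in the Discussion at face value could size a trial on a figure that is neither the cohort rate nor the control rate.

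**Working it through.** **What the plan produces.** There is no event rate, testing fraction or sizing calculation for these outcomes in the protocol to reproduce. Reading 2.3 with 2.5:

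- An untested patient has missing outcome data and is excluded, so the rate is events / tested.
- No routine-care event rate is produced: 2.2 puts HPI monitoring in every patient, and the two comparisons in 2.3 are of hypotension.

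**Inputs for the illustration (all assumptions).** Two-sided alpha 0.05, power 80%, relative reduction 25%, so q = 0.75p. Size per arm:

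n = (1.960 + 0.842)² × [p(1−p) + q(1−q)] / (p−q)²

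**1. Selective testing, risk differing between tested and untested.** Assume risk 15% in tested and 5% in untested patients.

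- 40% tested: cohort rate = 0.4 × 0.15 + 0.6 × 0.05 = 9%. Planned on 15%: n = 1,269. Needed at 9%: n = 2,246. Ratio 1.77; the trial of 1,269 per arm has about 56% power.
- 90% tested: cohort rate = 0.9 × 0.15 + 0.1 × 0.05 = 14%. Needed: n = 1,374. Ratio 1.08.

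**2. Selective testing, probability of testing differing by event.** Assume a true rate p = 10% (n = 2,002 per arm). With testing probability a in patients with the event and b in those without, the tested-only rate is pa / [pa + (1−p)b].

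| a / b | tested-only rate | n planned per arm | needed / planned | true power |
|---|---|---|---|---|
| 50% / 50% | 10.0% | 2,002 | 1.00 | 80% |
| 90% / 60% | 14.3% | 1,343 | 1.49 | 63% |
| 80% / 40% | 18.2% | 1,013 | 1.98 | 51% |

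A more extreme mix (80% / 20%) gives 30.8%, n = 519 and a ratio of 3.9. I treat that as an outer case. In the first row there is no bias, only lost precision: the 95% CI half-width, 1.96 × √(0.1 × 0.9 / m), goes from 2.2 points at m = 700 to 3.1 at m = 350.

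**3. Missing control rate.** Suppose the HPI rate is truly 10% and the relative risk 0.75. The control rate is then 0.10 / 0.75 = 13.3%, and 13.3% against 10% needs 1,453 per arm. Using 10% as the control rate gives 2,002, which is 1.38 times too many.

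**4. Both together.** With a true HPI rate of 10% and testing of 90% / 60%, the planner sees 14.3% and, using it as the control rate, plans 1,343 per arm where 1,453 are needed (ratio 1.08). The two faults nearly cancel here, by chance.

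**5. What the testing fraction decides.** If 10% of tested patients have the event and a share t is tested, the cohort rate lies between 0.1t and 0.1t + (1−t): 9% to 19% at t = 90%, 5% to 55% at t = 50%, 3% to 73% at t = 30%.

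**6. Death and arrest.** These do not depend on laboratory testing. Precision with 700 patients (exact 95% CI, assumed counts): 7 events, 0.40% to 2.05%; 14 events, 1.10% to 3.33%; 21 events, 1.87% to 4.55%.

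**The case against.** The registry's stated aim is to describe intraoperative hypotension. Trial planning occupies the closing sentences of one Discussion paragraph, and the clinical outcomes are labelled exploratory. No registry analysis rests on the criticised sentence. The protocol nowhere says that testing follows risk, and Table 2 schedules laboratory values both at baseline and after surgery. Testing could be close to complete, particularly for creatinine, in which case the bias is small. An HPI-cohort rate is also a legitimate sizing input once it is combined with an outside control rate or an assumed relative effect. Finally, details of denominators and sensitivity analyses usually belong in an analysis plan, which is not shown.

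Most of this stands, and it limits the point. Trial planning is not a main use of the registry, selective testing is a possibility and not an established fact, and the rates are not worthless. What remains is the text itself. It promises rates fit for robust sizing without qualification, while the measurement and missing-data rules that it does state yield tested-only rates. The concession on power concerns the effect of HPI, not the validity of the rates. The complete-case rule is written down, so the denominator is not simply left to another document.

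**Conclusion.** The point holds as a claim that is too strong for what the plan will deliver on the two laboratory outcomes. The size of the error is unknown because the protocol gives neither event rates nor testing fractions. Under the assumptions above, selective testing alone makes a planned trial too small by a factor from about 1.0 to about 2. Use of the HPI rate as the control rate makes it about 1.4 times too large at a relative risk of 0.75.

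A reader might infer that the promised rates must lead to an undersized trial. The documents do not support that: the direction depends on how testing relates to risk, on whether untested patients are excluded or counted as event-free, and on how the control rate is chosen. A reader might also extend the testing problem to death, re-admission and cardiac arrest. These have 30-day follow-up, so for them only precision and the missing control rate matter. The description of hypotension is not touched.

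**What to change.** Recruitment and follow-up are complete, so the change is to analysis and wording.

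1. For myocardial injury and for kidney injury separately, report tested/total overall and by centre.
2. In place of a complete-case rate alone, give the tested-only rate with 95% CI together with bounds that count all untested patients first as without and then as with the event. A rate weighted for the probability of being tested is an optional sensitivity analysis.
3. Give 95% CIs for death and for the cardiac arrest/death composite.
4. Reword the sentence in the Discussion along these lines: the event rates describe HPI-monitored patients; those for myocardial and kidney injury depend on routine testing and are reported with the share tested; a routine-care control rate for a randomised trial must come from another source.

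The cost is a modest extra analysis of data already collected and one revised sentence. The downside is wider, less favourable ranges, which may be uninformative for an outcome with a low testing fraction. That would itself tell planners not to rely on the rate.

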## 4. Trial Status

The protocol version is 1.4 with an effective date of 19 May 2022. Patient recruitment began in September 2021 and was completed in May 2022. The 30-day follow-up was completed in June 2022.

